### Statistical analyses

All analyses will be performed using the IBM Statistical package for the Social Science (SPSS) version 22 (IBM Corp., Armonk, NY USA) and STATA version 12.1 (StataCorp LP, Texas, USA). Descriptive statistics (e.g. frequencies, percentages, means and standard deviations or medians and (interquartile) ranges) will be generated for all socio-demographic and clinical characteristics and outcome measures. Chi-square tests, independent *t*-tests and Mann-Whitney tests (in case of non-normality of the measure) will be used to analyze whether randomization resulted in comparable patient groups. Analyzes will be performed according to the intention-to-treat principle. A *p*-value < .05 will be considered significant.

Independent *t*-tests will be used to measure differences in swallowing quality (SWAL-QOL), speech quality (SHI), shoulder function (SDQ) and quality of life (EORTC QLQ-C30 and H&N35) between the intervention and control group at follow-up measurements. Linear mixed models and generalized estimating equations, with fixed effects for group and measurement and their two-way interaction and a random effect for subject, will be used to compare longitudinal changes in both groups over time.

An incremental cost utility ratio (ICUR) will be calculated measuring the cost per gained quality-adjusted life year (QALY). The ICUR will be calculated by dividing the incremental costs by the incremental QALYs, using the formula: ICUR = (C_int_ - C_con_)/(QALY_int_ - QALY_con_). Total costs will be calculated using a societal perspective, including intervention costs, direct medical, direct non-medical and indirect non-medical costs. Direct medical and non-medical costs will be calculated by multiplying resource use by integral cost prices as presented in the CVZ guideline on cost studies [43]. Indirect non-medical costs will be calculated using the friction cost approach as recommended in the CVZ guideline [43]. Total QALYs will be calculated by using the utility scores linked to the various health states of the EQ-5D [40]; in essence the length of time a patient spends in a particular health condition is weighed by the corresponding utility. Missing data on direct medical, direct non-medical and indirect non-medical costs measured using the cost questionnaire and utilities measured using the EQ-5D will be imputed using multiple imputation. If necessary, the estimates of the cost difference, the QALY difference and the ICUR will be corrected for differences in baseline characteristics between the two groups. Since follow-up of the study is less than 1 year, we will neither discount costs nor effects. To assess uncertainty surrounding the findings, 5000 bootstrapped replications will be calculated and presented on a cost-utility plane. In addition, ICUR acceptability curves will be presented and sensitivity analyses will be performed focusing on uncertainty surrounding most important cost items.

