**Fig. 2 Fig2:**
[figure not shown]
Screenshot self-help exercise program

Patients randomized to the intervention group will be invited by their speech therapist or nurse practitioner/specialist for a consultation of half an hour in the hospital during which the patient will be instructed on how to perform the prescribed exercises. Following baseline consultation, patients are asked to perform the exercises at home, three times a day for 12 weeks, using the written instructions, images and videos of the prescribed exercises built into the online application of ITwC or a booklet plus DVD. The prescribed exercises and intensity of the exercises are fixed. The entire exercise protocol takes approximately 10–15 min a time.

To enhance exercise adherence, patients are asked to fill out a diary during the 12 week period. In addition, patients will be coached on a weekly basis by their speech therapist or nurse practitioner/specialist via e-mail or telephone. During these coaching sessions, patients will be asked on their general well-being and exercise performance. The speech therapist or nurse practitioner/specialist will take notes of these sessions in order to assess barriers and facilitators of adherence to the exercise program.

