#### Primary outcome measure

The primary outcome measure of this study is the swallowing quality of life questionnaire (SWAL-QOL). The SWAL-QOL is a 47-item patient-reported outcome measure that consists of ten different quality of life domains namely Food selection (two items), Eating duration (two items), Eating desire (three items), Fear (four items), Burden (two items), Mental health (five items), Social functioning (five items), Communication (two items), Sleep (two items) and Fatigue (three items). Furthermore, a symptom scale (14 items) is included. Based on the 30-items of the first seven mentioned quality of life domains a total SWAL-QOL score can be calculated. All SWAL-QOL scales range from 0 to 100, a higher score indicates more impairment. Finally, three separate questions on nutrition intake (normal, soft, pureed, mostly tube feeding, only liquids, tube feeding solely), liquids intake (all liquids, thick liquids, very thick liquids, thickened liquids, no liquids), and general health (poor, moderate, good, very good, excellent) are included. The SWAL-QOL has been translated into Dutch and validated for patients with head and neck cancer [33] and laryngeal cancer [8].

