### Sample size

In a previous study of Rinkel et al. [8] a standard deviation of 21 on the SWALQOL, the primary outcome measure in this study, was found. In addition, a difference in improvement of 12 points was found to be clinically meaningful. Based on a power of 80 %, a significance level of 5 % and a standard deviation of 21, in total 100 patients are needed (50 patients per intervention arm), to demonstrate a difference in improvement of 12 points between the intervention and control group at 6 months follow-up. Results will be analyzed according to the intention-to-treat principle and all drop-outs, when possible, will be approached for follow-up measurements.

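### SWAL-QOL is tied by name only to follow-up t-tests that ignore earlier scores; the mixed model already planned should be declared the primary 6-month analysis

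*Protocol article*

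**What the plan says.** - **Primary outcome measure:** "The primary outcome measure of this study is the swallowing quality of life questionnaire (SWAL-QOL"). Scores run from 0 to 100, and higher means worse.
- **Sample size:** the trial is sized "to demonstrate a difference in improvement of 12 points between the intervention and control group at 6 months follow-up". The same section commits to intention-to-treat and to approaching drop-outs for follow-up where possible.
- **Statistical analyses, effectiveness:** "Analyzes will be performed according to the intention-to-treat principle". SWAL-QOL, SHI, SDQ and the EORTC scales are compared between arms by independent t-tests at follow-up. The next sentence plans linear mixed models and GEE, with group, measurement, their interaction and a random subject effect, to compare change over time. That sentence names no outcome. Neither analysis is called primary.
- **Statistical analyses, cost-utility:** missing cost data and "utilities measured using the EQ-5D will be imputed using multiple imputation". No handling of missing SWAL-QOL scores is stated.
- **Self-help exercise program:** in the intervention arm, "patients are asked to perform the exercises at home, three times a day for 12 weeks", with a diary and weekly coaching. The control arm has no comparable task.

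**The concern.** Three analyses with different missing-data assumptions are listed for the repeated outcomes, and the primary outcome is linked by name to the one that uses least of the data. A patient with baseline and 3-month scores but no 6-month score contributes nothing to the 6-month t-test. If such patients differ between arms, the comparison is no longer the one that randomisation set up, and the intention-to-treat label does not repair it.

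Different drop-out by arm is plausible because only one arm has a demanding 12-week task and weekly contact. The Discussion itself reports that high drop-out limited the power of an earlier swallowing-exercise trial. At stake is whether the main effectiveness estimate refers to all randomised patients or to those who returned the last questionnaire.

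**Working it through.** **1. The plan's own figure.** Inputs from Sample size: difference 12, SD 21, power 80%, significance level 5%. Sidedness is not stated; two-sided reproduces the figure.

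n per arm = 2 × (1.96 + 0.842)² × 21² / 12² = 2 × 7.85 × 3.0625 ≈ 48.1, so 49 per arm and 98 in total. With the noncentral t distribution n = 49.05, so 50 per arm and 100 in total, as the plan states. The figure is therefore a two-sample t-test calculation for analysed patients.

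**2. Which scores each method uses.**

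| Method | Patients used at 6 months | Assumption about missing scores |
|---|---|---|
| Independent t-test | only those with a 6-month score | no difference between arms in how loss relates to the score |
| Unweighted GEE | all observed visits | generally missing completely at random |
| Likelihood mixed model | all observed visits | missing at random, given a suitable covariance model |

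**3. Size of the possible bias.** The article gives no drop-out rate, correlation or mechanism, so all of these are assumptions. Set-up: 400,000 simulated patients per arm; visits at baseline, 3 and 6 months; SD 21; equal correlation of 0.5 or 0.7 between visits; true effect −12 at 3 and 6 months (negative favours exercise). Loss of the 6-month score follows a logistic model, with log-odds rising by 1 per SD of worse score where loss is score-dependent, and an intercept set to give the stated rate. The t-test estimate is the difference in observed 6-month means. The missing-at-random estimate regresses the 6-month score on the baseline and 3-month scores within arm and averages the predictions over all patients. It stands in for a likelihood mixed model.

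| Assumed loss (intervention / control) | Loss depends on | t-test | Missing-at-random estimate |
|---|---|---|---|
| 20% / 20%, same mechanism | any one visit's score | −12.0 to −12.1 | −12.0 to −12.1 |
| 20% / 20%, score-dependent in intervention arm only | baseline or 3-month score | −13.8 to −14.6 | −11.9 to −12.0 |
| 30% / 10%, score-dependent in both arms or intervention only | baseline or 3-month score | −13.7 to −15.7 | −12.0 to −12.1 |
| the two unequal patterns above | unseen 6-month score | −15.4 to −17.2 | −13.6 to −15.6 |

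Where loss differs by arm and depends on earlier scores, the t-test is off by 13.7 − 12 = 1.7 to 15.7 − 12 = 3.7 points. That is 1.7/12 = 14% to 3.7/12 = 31% of the target difference. With 40 patients left per arm, the standard error is about 21 × √(2/40) = 4.7 points, so the bias is 1.7/4.7 ≈ 0.4 to 3.7/4.7 ≈ 0.8 standard errors.

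**4. Second check with no true effect.** 4,000 trials per scenario, 50 per arm, correlations 0.6 to 0.7, 10% random loss in control. Intervention loss was 20.0%, 21.1% or 24.5%, rising with the 3-month score. Complete-case bias was −1.7, −2.4 and −3.6 points respectively. Regression on baseline and 3-month scores gave 0.04, −0.01 and 0.01.

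**5. Direction.** These scenarios place the heavier or more selective loss in the intervention arm. Exchanging the arms reverses the sign of the bias.

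**The case against.** The strongest reply is that the remedy is already in the plan. The sentence after the t-tests provides linear mixed models, which keep patients who miss a visit and need no imputation. The sample size is expressed as a difference in improvement, which matches a longitudinal model at least as well as a t-test at one visit. A reader might infer that the primary effect will be estimated on completers only, or that SWAL-QOL has no valid method for missing scores. The article supports neither, because it never says the t-test is primary and it does plan the mixed model. Nor is limiting imputation to economic data an error in itself; further handling of clinical scores may sit in the full protocol or analysis plan.

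There are also safeguards. Drop-outs are to be approached for follow-up and reasons for drop-out recorded. A patient who stops exercising can still return questionnaires. The Discussion expects the weekly contact to help retain patients in the program. A reader might infer that the bias must favour exercise; since coaching could equally retain intervention patients, that does not follow.

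These arguments narrow the point, but they leave the mixed model's role undeclared while SWAL-QOL is named only beside the t-tests. Approaching drop-outs where possible does not say how the remaining gaps are analysed.

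**Conclusion.** The point holds in limited form. The article commits to intention-to-treat, assigns the primary outcome by name to a test that discards earlier scores, and lists a better method next to it without giving it priority. The possible bias is about 2 to 4 points in either direction, conditional on assumed loss of 20% to 30% in the intervention arm that differs between arms in rate or mechanism and depends on earlier scores. With the same rate and mechanism in both arms it is essentially zero. If loss depends on the unseen 6-month score, the mixed model is biased too, though less than the t-test in the scenarios examined. The change is worth making because it is nearly free, not because bias has been shown to be likely.

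**What to change.** State in Statistical analyses that the primary analysis is the 6-month group contrast from the likelihood linear mixed model, fitted to all observed SWAL-QOL scores (baseline, 3 and 6 months) of all randomised patients. Keep the t-tests as descriptive or supportive. If GEE is retained, do not let it carry the primary conclusion in its unweighted form.

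Optionally, add a sensitivity analysis for scores missing not at random, for example by worsening the assumed scores of intervention patients lost to follow-up over a range of 0 to 12 points. The mixed model does not remove that type of bias.

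The cost is a sentence or two of wording. The model is already planned, no new data are needed, and only the optional sensitivity analysis adds modest programming.

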## Methods

### Design

This study is a prospective multi-center randomized controlled trial with two parallel groups, comparing an intervention group to a control group with equal (1:1) randomization. Patients will be recruited from various head and neck cancer centers in the Netherlands in which TLs are performed. Patients in all participating centers who are found eligible will be asked to participate in this study by their treating head and neck surgeon, speech therapist or nurse specialist/practitioner at the last consultation prior to discharge, at follow-up visit or by mail plus telephone. After signing informed consent, patients will be randomly assigned to the intervention or control group. The baseline assessment takes place before randomization, with follow-up assessment immediately after the intervention or control period (i.e. at 3 months follow-up) and at 6 months follow-up (Fig. 1). Reasons for drop-out will be registered. This study has been approved by the Medical Ethics Committee of the VU University Medical Center.

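### Two analyses of the 6-month SWAL-QOL are planned, neither is named as primary, and neither conditions on the baseline score already collected

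*Protocol article*

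**What the plan says.** All references are to the Methods of the protocol article.

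- **Sample size.** The aim is "to demonstrate a difference in improvement of 12 points between the intervention and control group at 6 months follow-up". The inputs are "Based on a power of 80" %, "a significance level of 5" %, and an SD from an earlier study, in which "a standard deviation of 21 on the SWALQOL, the primary outcome measure in this study, was found". The result is 100 patients, 50 per arm.
- **Design.** "The baseline assessment takes place before randomization, with follow-up assessment immediately after the intervention or control period" and again at 6 months. Every patient should therefore have a pre-randomization SWAL-QOL score.
- **Statistical analyses, first method.** Independent t-tests "will be used to measure differences in swallowing quality (SWAL-QOL), speech quality (SHI), shoulder function (SDQ) and quality of life" between the arms at the follow-up assessments. No covariate and no change score is mentioned.
- **Statistical analyses, second method.** The next sentence adds linear mixed models and generalized estimating equations with group, measurement and their interaction as fixed effects and a random subject effect, to compare how the arms change over time.

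The section does not rank the two methods for the primary outcome at 6 months.

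**The concern.** The sample-size paragraph speaks of improvement, which is a change from baseline. The first analysis listed compares scores at follow-up and does not use baseline. The second does concern change, provided baseline is one of its measurements, as the wording implies. A reader cannot tell which result will decide the trial.

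Two things are at stake. The first is precision: a baseline measurement of the primary outcome is available, and neither method conditions on it. The second is clarity. The two methods can give different answers from the same data, and with no ranking the choice stays open until the results are known.

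**Working it through.** **Inputs**

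- Difference 12 points, SD 21, power 80%, significance level 5%: Sample size section.
- Allocation: "comparing an intervention group to a control group with equal (1:1) randomization", Design section.
- Sidedness: not stated. Two-sided is assumed, because it reproduces the plan's figure and one-sided does not.
- Correlation rho between baseline and 6-month SWAL-QOL: not in the article. Assumed values are 0.3, 0.5 and 0.7.
- SD of 21 taken as the SD of scores, equal at baseline and 6 months. This is the natural reading, but the article does not state it.

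**Step 1. Reproduce the plan's figure.**

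Normal approximation: n per arm = 2 × (1.96 + 0.842)² × 21² / 12² = 48.1, rounded up to 49, or 98 in total. With the exact two-sample t-test (noncentral t), 49 per arm gives 79.96% and 50 per arm gives 80.8%, so 100 in total. A one-sided 5% test would need 38 per arm, 76 in total. The stated 100 is therefore reproduced by a two-sided t-test with SD 21.

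**Step 2. SD that applies to each analysis.**

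- Follow-up score t-test: SD = 21 for any rho.
- Change-score contrast: SD = 21 × √(2(1 − rho)). In complete data, the 6-month group-by-measurement contrast of the stated mixed model is in effect this comparison, if baseline is one of the measurements.
- Baseline-adjusted comparison (ANCOVA): SD = 21 × √(1 − rho²).

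The change-score SD equals 21 only at rho = 0.5.

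**Step 3. Power at 50 per arm, difference 12, two-sided 5%, exact t.**

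| rho | Follow-up t-test | Change SD | Change-score power | Adjusted SD | Adjusted power |
|---|---|---|---|---|---|
| 0.3 | 80.8% | 24.8 | 66.7% | 20.0 | 84.3% |
| 0.5 | 80.8% | 21.0 | 80.8% | 18.2 | 90.4% |
| 0.7 | 80.8% | 16.3 | 95.5% | 15.0 | 97.7% |

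For rho between 0 and 1, the adjusted SD is smaller than both of the others. Using 97 instead of 98 degrees of freedom for ANCOVA leaves these figures unchanged to one decimal.

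**Step 4. Chance baseline imbalance.**

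The standard error of the baseline difference is 21 × √(2/50) = 4.2 points. Given an imbalance of that size, the expected shift in the unadjusted 6-month difference is rho × 4.2: 1.3, 2.1 and 2.9 points at rho 0.3, 0.5 and 0.7. At rho 0.5 that is 2.1/12, about a sixth of the target. A change score moves the other way, by (1 − rho) × 4.2, which is also 2.1 points at rho 0.5. ANCOVA removes this component.

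**Step 5. What leaving two tests unranked means.**

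The follow-up and change-score estimates of the 6-month difference correlate √((1 − rho)/2): 0.59, 0.50 and 0.39 at rho 0.3, 0.5 and 0.7. By bivariate normal approximation with a true effect of 12 points, one is significant and the other is not in about 26%, 21% and 19% of trials. With no effect, at least one is significant in about 9% of trials, against 5% for a single named test.

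**The case against.** Several stronger readings are tempting, and the article does not support them.

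- **That the plan ignores baseline.** It does not. The mixed models and GEE follow the t-tests directly, are meant to compare change over time, and use baseline if it is one of the measurements. The t-test is one of two stated analyses.
- **That the power calculation refers to something the t-test cannot estimate.** Baseline precedes randomization, so the expected baseline difference is zero. The difference in follow-up means and the difference in mean change then have the same expectation. The t-test is unbiased for the difference in improvement and keeps its type I error.
- **That the SD is the wrong one.** The article ties 21 to the questionnaire without saying whether it is of scores or of change, and the source is not at hand. If it is of scores, it is the right SD for the follow-up t-test.
- **That imbalance passes whole into the result.** Only the fraction rho of it does. The t-test's standard error already allows for chance imbalance. Randomization is also stratified by time since laryngectomy, neck dissection and indication, though not by baseline swallowing score.

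It can also be said that the choice of contrast, and whether baseline means are constrained, is detail an article may leave to a fuller document. That is fair for the mixed model taken alone, and it is why the model's form is not called a fault here. It does not remove what the article itself states: an unadjusted t-test listed first for the primary outcome, beside a second method with a different precision.

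Finally, the gain from adjustment is power above the planned 80%, and its size depends on an assumed correlation. A change-score contrast falls short of 80% only when rho is below about 0.5. Both points stand and limit the severity.

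**Conclusion.** The point holds as a should-fix matter of efficiency and clarity. The sample size is sound: 50 per arm gives 80.8% power for the follow-up t-test if 21 is the SD of scores. Both stated analyses are valid, but neither is designated as the primary 6-month test and neither is as precise as conditioning on baseline. At rho 0.3, 0.5 and 0.7, adjustment adds roughly 4, 10 and 17 percentage points of power over the follow-up t-test. Over the change-score contrast it adds roughly 18, 10 and 2 points.

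These figures rest on an assumed rho, equal score SDs of 21 at both times, two-sided testing and complete data at 50 per arm. The direction of the comparison holds for any rho between 0 and 1; the size does not.

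**What to change.** 1. In Statistical analyses, replace the follow-up t-tests with one named primary test of the SWAL-QOL total at 6 months. Either of these would serve: ANCOVA of the 6-month score on arm and baseline score, or the mixed model with the arms' baseline means constrained equal and the 6-month arm contrast as the test.
2. Use the same baseline-adjusted form for the SHI, SDQ and EORTC scales.
3. In Sample size, word the target as a 12-point between-group difference at 6 months, adjusted for baseline. State whether the SD of 21 is of scores or of change.

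The number of patients need not change. The cost is some rewording, a few lines of code and one residual degree of freedom, with no new data.

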### Randomization

Patients will be randomized to the intervention or control group by an independent person, stratified for 1) time since TL (≤6 months after TL vs. > 6 months after TL) to distinguish patients who are recently treated and who may in some cases receive postoperative (chemo)radiation from patients who completed their treatment longer ago; 2) neck dissection (not treated with a neck dissection versus treated with a neck dissection); and 3) TL indication (primary TL or salvage TL) in blocks of two and four using an automatically created randomization list. Although this is a multicenter study, we chose not to stratify for study center, because head and neck cancer care is mainly centered in the University Hospitals in the Netherlands and highly protocolled via the Dutch Head and Neck Oncology Cooperative Group (NWHHT).

Patients randomized to the intervention group will be provided access to the guided self-help exercise program targeting speech, swallowing and shoulder problems built into the application ITwC as well as the self-care education program. Patients randomized to the control group will, in addition to usual care, also be provided access to the self-care education program, since we aim to investigate the effectiveness of the guided self-help exercise program only.

The guided self-help program ITwC will be provided by Internet [32] or as booklet plus DVD. Patients can choose themselves between these two formats. Both formats contain the same content (i.e. the same written instructions, images and videos are available).

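### The follow-up t-tests ignore the three factors used to stratify randomisation; if those factors predict the outcome, the tests are conservative and some power is lost

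*Protocol article*

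**What the plan says.** The Randomization section of the protocol article sets three two-level stratification factors, which give eight strata. The first is time since TL, split at 6 months. The other two are "neck dissection (not treated with a neck dissection versus treated with a neck dissection); and 3) TL indication (primary TL or salvage TL"). Allocation uses blocks of two and four. A reason is given only for time since TL: it separates recently treated patients, some of whom may still be receiving postoperative (chemo)radiation. Centre is deliberately left out: "Although this is a multicenter study, we chose not to stratify for study center".

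The Statistical analyses section names two effectiveness analyses. Independent t-tests compare the arms at the follow-up measurements on SWAL-QOL, SHI, SDQ and the EORTC scales. Mixed models and generalised estimating equations compare change over time, "with fixed effects for group and measurement and their two-way interaction and a random effect for subject". No stratification factor appears in either. The only correction for baseline characteristics is the one for the cost and QALY estimates. It applies only if judged necessary, and it does not name these factors.

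The Sample size section plans "to demonstrate a difference in improvement of 12 points between the intervention and control group at 6 months follow-up", with "in total 100 patients are needed (50 patients per intervention arm").

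**The concern.** Randomising in small blocks within strata forces the arms to be nearly balanced on the three factors. Any outcome variation between strata then largely drops out of the difference between arms. An independent t-test does not know this. It computes its standard error as if allocation had been simple, so variation that the design has removed stays in the denominator. If the factors are related to the outcome, confidence intervals are wider than they need be, the test runs below its nominal 5%, and power falls short of what the same patients could give.

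A relation is plausible. Patients within 6 months of TL may still be under treatment, and the article's Background links neck dissection to shoulder problems, which the SDQ measures and which are tested in the same way. At stake is efficiency in a trial of 100 patients.

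**Working it through.** **Inputs.** From the Sample size section: "Based on a power of 80 %, a significance level of 5 % and a standard deviation of 21", a difference of 12 points, and 50 per arm. From Design: 1:1 allocation. Sidedness is not stated. The share of outcome variance explained by the three factors, R², is not given either, so a range of 0 to 0.30 is assumed.

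**The plan's own figure.** Two-sided, normal approximation: n per arm = 2 × (21/12)² × (1.96 + 0.842)² = 48.1, so 49 per arm and 98 in total. The exact t-test needs 49.05 per arm, rounded up to 50, or 100 in total. The stated size reproduces. A one-sided test would need 38 per arm and does not match.

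**Follow-up t-test under stratified allocation.** The t-test's standard error is SE = 21 × √(2/50) = 4.2. The true standard deviation of the estimate is 4.2 × √(1 − R²). Hence:

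- actual type I error = 2 × [1 − Φ(1.96/√(1 − R²))]
- power unadjusted = Φ[(12/4.2 − 1.96)/√(1 − R²)]
- power adjusted = Φ[12/(4.2 × √(1 − R²)) − 1.96]

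Worked at R² = 0.20, where √0.80 = 0.894:

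- type I error: 1.96/0.894 = 2.19, which gives 2.8%
- power unadjusted: (2.857 − 1.96)/0.894 = 1.003, which gives 84.2%
- power adjusted: 2.857/0.894 − 1.96 = 1.234, which gives 89.2%

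| Assumed R² | SE too wide by factor | Actual type I error | Power unadjusted | Power adjusted |
|---|---|---|---|---|
| 0 | 1.00 | 5.0% | 81.5% | 81.5% |
| 0.05 | 1.03 | 4.4% | 82.1% | 83.4% |
| 0.10 | 1.05 | 3.9% | 82.8% | 85.4% |
| 0.20 | 1.12 | 2.8% | 84.2% | 89.2% |
| 0.30 | 1.20 | 1.9% | 85.8% | 92.7% |

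**Simulation check.** The simulation used 100 patients, eight strata, blocks of two and four, and 6,000 runs per setting. Assumed factor prevalences were 30%, 60% and 50%, and the assumed correlation between time points was 0.5. At R² = 0.20 the t-test's mean SE was about 4.2 against a true 3.80, type I error was 3.1%, and power was 83.2% unadjusted against 88.6% adjusted. At R² = 0.10 type I error was 3.8%, and power was 81.6% against 84.1%. At R² = 0 there was no material difference.

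**Longitudinal model.** Here the treatment effect is the group-by-measurement interaction, a within-patient contrast. Factor effects that are constant over time cancel from it. In one complete simulated data set with three measurements, the interaction estimates were −13.0859 and −16.4712 with SE 3.7696. Adding the three factors as main effects left both estimates and the SE identical. In the two-arm simulation of change from baseline, with factors that shift level but not change (R² = 0.20), the mean SE was 4.19 against a true 4.16 to 4.18. Type I error was 4.9%, and power was 81.4% unadjusted against 81.2% adjusted. Only factors that predict change make a difference here, and only factor-by-measurement terms capture that.

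**The case against.** The strongest reply is that nothing in the plan is invalid. The error is in the safe direction, and unadjusted power at 50 per arm is at least 81% whatever R² is. The trial is sized on a difference in improvement, and for change from baseline nothing is lost unless the factors predict change and not just level. The article is also a condensed account, and covariate sets are often fixed in an analysis plan.

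Most of this stands, and it limits the size of the point. The last part does not remove it. The article names an unadjusted test and lists the longitudinal model's terms, so this is a stated analysis that does not match the stated design. The margin over 80% also assumes that all 100 patients are evaluable, and the Sample size section makes no allowance for drop-out. By the formulas above with R² = 0.20, assumed drop-out of 10%, 15% or 20% gives power of about 80%, 77% or 75% unadjusted, against 86%, 84% or 82% adjusted.

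A reader might infer more than the document supports:

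- **That the factors are known to be prognostic, so standard errors are certainly too wide.** The article never says they predict SWAL-QOL, gives no figure, and explains only the choice of time since TL.
- **That the longitudinal model's standard error is too wide as well.** The check shows otherwise for factors that affect level only.
- **That centre should be added as a random effect.** The article gives a reason for not stratifying by centre: care is centralised and protocolled. It reports no centre variance. A centre intercept shared by both arms would not model coaching that only one arm receives.

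**Conclusion.** The point holds for the follow-up t-tests, conditionally. The design stratifies on three factors and the stated comparisons ignore them. If the factors explain 5% to 30% of outcome variance, the t-test's SE is 1.03 to 1.20 times too wide. The cost against an adjusted analysis is about 1 to 7 percentage points of power; at R² = 0 it is nil. The figures rest on the assumed R², the planning SD of 21, a two-sided 5% level and complete data. Type I error is not inflated, no bias follows, and the planned 80% is not undercut before drop-out. Severity is minor to moderate: a cheap gain in precision, not a flaw that threatens the conclusion.

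**What to change.** Replace the follow-up t-tests with a linear model containing group, the three stratification factors and the baseline value of the outcome. In the longitudinal model, add the three factors together with their interactions with measurement; main effects alone would leave the treatment contrast as it is in complete data. Leave centre out.

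The baseline term may itself be worth more than the factors. With residual SD = 21 × √(1 − ρ²) and an assumed baseline-to-follow-up correlation ρ of 0.3, 0.5 or 0.7, power at 50 per arm is 85%, 91% or 98%. The two gains overlap and should not be added, because baseline will absorb part of what the factors explain.

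The cost is a few extra parameters with about 100 patients, and changes to wording and code only. Recruitment, data collection and visits are unaffected.
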